#### Students

Students of participating schools are included in the study if they meet the criteria for extensive medical absenteeism, which is based on the MASS intervention at pre-vocational secondary education schools (i.e. reported sick for at least four times in 12 weeks or reported sick for more than six consecutive school days). We expect to include a total number of 480 students in the study with an equal distribution between the control and intervention group (see Fig. 1).

**Fig. 1 Fig1:**
[figure not shown]
Flow chart of the MASS study

### Procedure

Participating schools are visited by the Erasmus MC researchers to explain the procedure of the study. The schools (usually an appointed coordinator) select students meeting the inclusion criteria (i.e. reported sick for at least four times in 12 weeks or reported sick for more than six consecutive school days) and invite them to participate in the study. All students receive an information letter and leaflet with information about the study. They are asked to provide informed consent. Participants in the study are invited to complete the baseline questionnaire. The coordinator will send the filled-out questionnaires back to the researchers on a regular basis. For students aged younger than 18 years of age qualifying for participation, parents also receive an information letter and brochure about the study at home provided by school; these parents can object to participation in the study by their child. After 6 months, a follow-up questionnaire will be sent to the students. Students will receive either a hard-copy version, a digital version or both versions, depending on their preference.

Students in intervention schools who have a consultation with the YHC professional will be asked by the YHC professional to complete an additional short questionnaire after consultation. The YHC professionals themselves are also asked to fill out a short questionnaire after each consultation. All questionnaires are to be dropped in sealed envelopes in a drop box which will be located at an agreed upon location with the coordinator of the school. The coordinator will send the questionnaires back to the researchers on a regular basis.

Data will be processed in accordance with the agreed guidelines of the Dutch Data Protection Authority Intervention [30].

### Intervention

#### Intervention group: the MASS intervention

The MASS intervention designed for intermediate vocational education schools consists of five steps: an active approach by the school after the first sick report, a meeting between student and school, a YHC professional referral if needed, the actual YHC professional consultation, and the further monitoring of the medical absenteeism and reintegration of the student [31] (Table 1).

**Table 1 Tab1:** Description of the key steps of the MASS intervention

Step	Description
1	The school contacts the student actively in case of medical absence and asks about the context of the sickness report and condition of the student.
2	The school organizes a meeting with the student (and parents if student is <18 years old) in case of extensive medical absenteeism (criteria predefined by each individual school, apart from the MASS criteria).
3	The school refers the student to a YHC professional if considered to be needed.
4	A YHC consultation between student and YHC professional is organized
5	The school is responsible for monitoring the medical absenteeism and school-related implementation of the reintegration plan, if created.

*MASS* Medical Advice for Sick-reported Students

*YHC professional* Youth health care professional

The intervention focuses at two levels; the school level and the individual level. The implementation of the MASS intervention at school level includes agreements on how to actively monitor student absence, approach students with extensive medical absence by personal contact, request a consultation with the YHC professional, and arrange a follow-up for each student in the Care Advisory Team (CAT). The CAT includes social workers, attendance officer, YHC professionals, teachers and a Youth Care Office representative.

At an individual level students with extensive medical absenteeism will be identified by school and referred to YHC if needed. In the consultation, the YHC professional focuses on somatic, psychological and social factors potentially underlying the medical absenteeism (Table 2). Along with the student, and the parents if the student is younger than 18 years of age, a reintegration plan is formulated. Whichever reintegration plan is chosen, the YHC professional is accountable for the referral, the aftercare, communication with other care professionals, communication with the adolescent and monitoring the procedure accurately. All YHC professionals are trained in performing the MASS protocol [31].

**Table 2 Tab2:** Description of key elements of the YHC consultation

Element	Description
1	The YHC professional and the student conduct a problem analysis
2	The YHC professional analyses the underlying problems by use of the biopsychosocial model
3	The underlying causes of the medical absence are defined
4	The possibilities of preventing recurrence in the future are discussed
5	The possibilities for extra treatments by health care professionals or other supporting professionals are discussed
6	An action plan regarding reintegration will be created, if needed
7	The YHC professional is responsible for communicating, with the consent of the student, the reintegration plan to all other involved parties without violating his/her professional secrecy

*YHC professional* Youth health care professional

#### Control group: care as usual

The control group consists of students attending Intermediate Vocational Education schools that have not implemented the MASS intervention. They continue to provide care as usual using their current absenteeism policy. This generally consists of a referral to a YHC professional on request of the student, when accessible consultation of the CAT and referring to the school attendance officer when student is younger than 18 years old.

### Measurements

The following primary and secondary outcome measures were formulated:

Primary outcomes measures

➢ Duration of the medical absence in days within the last 12 weeks at T1 (in comparison with T0).

➢ Cumulative incidence of the medical absenteeism, measured during six months after determining the extensive medical absenteeism.

➢ Academic performances as measured by passing onto the next year or obtaining a basic educational qualification degree.

➢ The extent to which the chosen educational program matches the student’s interests.

Secondary outcome measures

➢ Biopsychosocial problems of intermediate vocational education students after determining the extensive medical absenteeism; it concerns medical, physical, emotional, and psychiatric problems (e.g. depression, anxiety, ADHD), housing, financial problems and contacts in criminal justice.

➢ Realised changes/adjustments in treatment policy by specialists and other involved healthcare professionals for students with depression, anxiety, ADHD and autism spectrum disorders.

Specific outcomes related to the care by YHC professionals.

➢ The extent to which the YHC professionals work in accordance with the MASS protocol assessed during consultation with the student.

➢ Perceived value of the MASS intervention according to the YHC professionals and the students.

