**Discussion:**

It is hypothesized that implementing the MASS intervention including a referral to a YHC professional on indication, will result in a lower level of medical absenteeism and a lower level of school drop outs among intermediate vocational education students compared to students receiving usual care. The study will provide insight in the effectiveness of the intervention as well as in factors moderating the intervention’s effectiveness.

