In 2012, the Medical Advice for Sick-reported Students (MASS) intervention was developed [19] to address medical absenteeism more actively within students attending pre-vocational secondary education, the school level preceding intermediate vocational education. The aim of the MASS intervention is to limit medical absenteeism by arranging appropriate care, educational adjustments and adequate support for students [21]. The intervention focuses on the factors associated with extensive medical absenteeism: somatic, mental and physical complains [9, 22–25], poor lifestyle [11] and psychological, family and social problems of sick-reported students [9]. The schools and the YHC professionals collaborate directly within the MASS intervention to design and monitor a management plan that aims to optimize students’ health and maximize students’ participation in school activities [19, 25] In an effect study Vanneste et al. found a reduction of 15.1% in medical absenteeism among pre-vocational secondary education school students after implementing the MASS intervention [19].

As students in pre-vocational secondary education schools often continue their education at intermediate vocational education schools, medical absenteeism might be associated with the same determinants in both groups of students. Despite potential similarities between intermediate vocational education and pre-vocational secondary education students, there are also clear differences that need to be taken into account in designing interventions. Students in intermediate vocational education schools, for instance, are generally aged between 15 and 25 years old. Furthermore, the level of medical absence is often larger at intermediate vocational education schools and its nature is often more complex due to underlying biopsychosocial factors and financial problems. As a result, the MASS intervention has been adapted for intermediate vocational education schools and is currently being applied at several schools in the Netherlands [26–28]. However, evidence for its effectiveness is thus far lacking.

The aim of this study is to evaluate the effectiveness of the MASS intervention at intermediate vocational education schools, with a focus on the efforts of the YHC professional, in terms of reducing students’ medical absenteeism and early dropping out of school. In addition, we will assess to what extent biopsychosocial and other factors may influence the effect of the intervention.

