## Methods/Design

### Study design

A controlled before-and-after study with a follow-up period of 6 months will be conducted. Students with extensive medical absence attending schools in which the MASS intervention has been implemented (intervention group) are compared to students attending schools in which the MASS intervention has not been implemented (control group).

The Medical Ethical Committee of Erasmus University Medical Centre Rotterdam has declared that the Medical Research Involving Human Subjects Act (also known by its Dutch abbreviation WMO) does not apply to this research protocol and issued a declaration of no objection (i.e. formal waver) for this study (MEC-2015-614). Therefore, the study can be carried out without further approval by an accredited research ethics committee.

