### Data collection

Data collection takes place during 1,5 academic school years. All students complete a questionnaire at baseline (T0) and after six months at follow-up (T1). In addition, students in the intervention group complete a questionnaire after consultation with a YHC professional. The YHC professional likewise completes a questionnaire after each consultation with a student in the intervention group. To measure the level of medical absenteeism, data is retrieved from the registration system from school.

The level of medical absenteeism is obtained from the *absenteeism registration system* from the school in numbers of hours during a period of 12 weeks before T0 and T1; and also during the six months period between T0 and T1. Schools also provide information on the support that was given by the school to the student i.e. school meetings, social work or appointments with the psychologist.

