### Statistical analyses

In order to evaluate effect of the effect of the intervention the scores on outcomes of both groups measured during follow will be compared, adjusted for baseline findings. For continuous outcome measures such as duration of the medical absenteeism and psychometric test results (multiple) linear regression analyses will be applied. Dichotomous outcomes, such as progressing into the next year or obtaining a basic educational qualification degree, will be evaluated by using a multiple logistic regression analysis.

The research condition will be included as an independent variable. Baseline values of the outcomes are added to the model as covariates. As students are clustered within school locations multilevel analyses will be applied.

Potential moderation of intervention effects by gender, family situation, ethnicity, psychosocial and psychiatric problems (depression, drug abuse, ADHD) is explored by adding an interaction term to the regression models. Stratified analyses will be performed when significant interactions (*p* < 0.10) are observed.

Experiences of students and YHC professionals with the different elements of the MASS intervention as performed by YHC professionals will be evaluated by performing descriptive analyses.

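### Early school dropout is in the aim and hypothesis but is not an outcome, and the academic outcome nearest to it is a yearly event with no assessment date in a six-month follow-up

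*Protocol article*

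**What the plan says.** The Background section states the aim as evaluating the intervention "in terms of reducing students’ medical absenteeism and early dropping out of school", and the Abstract (Background) says the same. The Abstract (Discussion) hypothesises less medical absenteeism and "a lower level of school drop outs among intermediate vocational education students" than under usual care.

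Measurements lists four primary outcomes, two secondary outcomes and two outcomes on the care given by youth health care professionals. None is dropout. The nearest is the third primary outcome: "Academic performances as measured by passing onto the next year or obtaining a basic educational qualification degree". The two absenteeism outcomes each carry a time window. This one carries none.

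On timing, Study design says "A controlled before-and-after study with a follow-up period of 6 months will be conducted", and Data collection says "All students complete a questionnaire at baseline (T0) and after six months at follow-up (T1"). The same section adds: "Data collection takes place during 1,5 academic school years". It lists what schools supply, namely absence hours and the support given to the student. Promotion or degree records are not on that list.

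Under Statistical analyses, the "scores on outcomes of both groups measured during follow will be compared, adjusted for baseline findings". The academic outcome gets its own sentence: "Dichotomous outcomes, such as progressing into the next year or obtaining a basic educational qualification degree, will be evaluated by using a multiple logistic regression". Dropout is not mentioned there.

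**The concern.** There are two linked problems.

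**Aim against outcome.** Not passing the year and leaving school are different events. A student who repeats the year counts as a failure on the academic outcome but has not dropped out. A student who passes can still leave afterwards. A logistic model of the academic outcome puts repeaters and leavers together, so its result cannot be read as an effect on dropout. The study could then report on half of its aim without having measured it.

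**Yearly event against a rolling six-month window.** Students enter once they meet the absence criterion and are measured again six months later. Promotion and graduation are decided at the end of a school year. For a student who enters early in the year, T1 can fall before any decision exists. The article does not say when or from which source the outcome is then read, so its value for that student is not fixed.

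**Working it through.** **1. The plan's own figure.** The only quantitative target is in Power considerations: 15 h of absenteeism, from 120 completers per group, intraclass correlation 0.10, 15 students per class, SD 30 h, one-sided alpha 0.05 and power 0.80.

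- Design effect: 1 + (15 − 1) × 0.10 = 2.4
- Effective size per group: 120 / 2.4 = 50
- Detectable difference: 30 × √(2/50) × (1.645 + 0.842) = 14.92 h

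The 15 h reproduces. It concerns absenteeism hours only and says nothing about the academic outcome or dropout.

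**2. Aim and hypothesis against outcomes and analysis.**

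| Element | Medical absenteeism | Early dropout |
|---|---|---|
| Aim (Abstract, Background) | yes | yes |
| Hypothesis (Abstract, Discussion) | yes | yes |
| Listed outcome (Measurements) | yes, two, each with a window | no |
| Named in Statistical analyses | yes | no |

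The Background section itself treats progression and dropout as separate quantities: 50% of entrants pass to the second year, and about 25% leave without a degree after five years. The horizons differ, so these two figures illustrate the distinction and do not measure the gap.

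**3. Share of students whose T1 precedes the year-end decision.** The article gives neither the start month nor the entry pattern, so the following are assumptions. Month 0 is the start of the school year, the decision comes at month Y (9.5 to 10.5), and entry is even in term time from month a over a one-year recruitment. T1 precedes the decision when entry is before month Y − 6, so

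share = (Y − 6 − a) / (Y − a)

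| First entry (a) | Y = 9.5 | Y = 10 | Y = 10.5 |
|---|---|---|---|
| 0, first day | 3.5/9.5 = 37% | 4/10 = 40% | 4.5/10.5 = 43% |
| 1.5 months | 2/8 = 25% | 2.5/8.5 = 29% | 3/9 = 33% |
| 2.8 months (full 12-week look-back within the year) | 0.7/6.7 = 10% | 1.2/7.2 = 17% | 1.7/7.7 = 22% |

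The widest range tried adds an 18-month recruitment.

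- Starting at month 0 with a = 0 and Y = 10.5, early entry is possible in two school years: (4.5 + 4.5) / (10.5 + 6) = 55%.
- Starting at month 5 with a = 2.8 and Y = 9.5: 0.7 / (4.5 + 6.7) = 6%.

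If the 1.5 academic years must also contain the last T1, recruitment can last only about one year, and the table applies (10–43%).

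**4. What that could mean for the academic outcome (illustration).** Assume a 50% pass rate in one group, one-sided alpha 0.05 and power 0.80. The detectable difference d solves

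d = [1.645 × √(2p̄(1 − p̄)) + 0.842 × √(p₁(1 − p₁) + p₂(1 − p₂))] / √n_eff

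- All 120 evaluable: n_eff = 50, d about 24 percentage points.
- 40% without a decision: 120 × 0.6 = 72 evaluable. With the design effect kept at 2.4, n_eff = 72/2.4 = 30 and d is about 30 points.
- If the missing students are spread evenly, the class size falls to 15 × 0.6 = 9, the design effect to 1 + 8 × 0.10 = 1.8, and n_eff is 72/1.8 = 40. Then d is about 26–27 points.

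**The case against.** The strongest reply is that the article never says the academic outcome is read at T1. That is correct. The six-month limit is inferred from Study design, Data collection and Statistical analyses. The 1.5 academic years of data collection contain at least one year-end, and schools already supply administrative data, so a year-end reading is compatible with the text. A bare missing date could also be left to a fuller document. What remains is that the only follow-up described need not contain the event, and that the list of school data omits promotion and degree records.

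It can also be said that passing or qualifying is an evident proxy for not dropping out, and that dropout is one of two aims. Both points stand. A proxy that scores repeaters and leavers alike still does not answer a question about leaving.

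A reader might go further in three ways that the documents do not support:

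- **That a large share of students get an automatically negative value.** No rule codes undecided students as failures, and the share depends on an entry calendar that is not given. Students must also accumulate absence before they qualify, which lowers it.
- **That the effect is confounded with entry month.** This needs entry timing to differ between groups. Participants and Procedure apply the same criterion and the same selection by schools to both. The school-specific criteria in the article concern meetings and referral, not study entry.
- **That the dropout hypothesis goes wholly unexamined.** The academic outcome bears on it in part.

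**Conclusion.** The point holds in two parts of different strength.

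The dropout part follows from the text alone. Dropout is one of two stated aims and part of the hypothesis, but it is neither a listed nor an analysed outcome, and the academic outcome is a partial proxy.

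The timing part is sound but inferred. A primary outcome that is decided yearly has no stated date or source, and the six-month follow-up can end before the decision for students who enter in roughly the first 3.5 to 4.5 months of the school year. Its size is an assumption throughout: about 25–43% under one-year recruitment with entry starting in the first weeks, as low as 10% if the full look-back must fall within the year, and 6–55% over all layouts tried. The documents do not establish that many students are affected, or that the groups are affected differently.

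This should be changed, because the repair is cheap and otherwise half of the aim has no measure of its own.

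**What to change.** 1. Take academic status for every consented student, including those who do not return the T1 questionnaire, from the school administration at the first academic year-end after T0.
2. Classify it as promoted or qualified, repeating, or left without a basic qualification.
3. Analyse left without a basic qualification as the dropout outcome in the multilevel logistic model already planned. Adjust for entry month, because the time from T0 to year-end varies.
4. If this is not done, remove dropout from the aim and hypothesis and describe the academic outcome as progression or qualification only.

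The cost is one extra extract per school and no further student contact. Results for early entrants arrive later, because their year-end falls after T1; late entrants reach the year-end before T1. Exposure time is also unequal: an early entrant has most of a year between T0 and the reading, a late entrant only weeks. The entry-month covariate handles that only in part, and the report should say so.

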#### Covariates

The covariates are chosen based on comparison of baseline characteristics of intervention and control students. Demographic information regarding the participating students is collected at baseline including ethnicity, SES score, attending school, educational level, and parenthood. Information on a number of known risk factors for school absenteeism are collected at baseline and during follow-up, including age, gender, smoking status, alcohol consumption (abstainer, up to >7 servings/week) and drugs abuse (abstainer, soft drugs, and hard drugs). Biopsychosocial problems concerning medical, physical, emotional, and psychiatric problems (e.g. depression, anxiety, ADHD), housing, financial problems and contacts in criminal justice are included as covariates. Level of physical activity is assessed at baseline and follow-up.

### Data collection

Data collection takes place during 1,5 academic school years. All students complete a questionnaire at baseline (T0) and after six months at follow-up (T1). In addition, students in the intervention group complete a questionnaire after consultation with a YHC professional. The YHC professional likewise completes a questionnaire after each consultation with a student in the intervention group. To measure the level of medical absenteeism, data is retrieved from the registration system from school.

The level of medical absenteeism is obtained from the *absenteeism registration system* from the school in numbers of hours during a period of 12 weeks before T0 and T1; and also during the six months period between T0 and T1. Schools also provide information on the support that was given by the school to the student i.e. school meetings, social work or appointments with the psychologist.

The *baseline questionnaire* (T0) contains the following measurements; socio-demographic characteristics, behavioral determinants, mental health conditions, and overall wellbeing. Data on socio-demographic characteristics of the students will be gathered, by including questions regarding gender, age, educational level, country of birth, parents’ country of birth, and home environment [32, 33]. Behavioural determinants are assessed by questions about school career, physical activity, financial situation, sexual behaviour, smoking, alcohol use and drug abuse. In addition, absenteeism is measured by using the questionnaire based on the questionnaires developed by Municipal Public Health Services and health institutes [34]. Mental health conditions are assessed by using the Centre for Epidemiologic Studies Depression scale (CES-D) [35] and the 12-item Short Form Health Survey (SF-12) to measure health-related quality of life [36]. The CES-D scale is a 20-item scale used to determine the clinical relevance of depression. Selected items will cover the main components of depressive symptoms such as depressed mood, guilt, feelings of inferiority, feelings of helplessness, despair, loss of appetite, sleep and psychomotor retardation [37–39]. The SF-12 questionnaire is used to measure Quality of Life [36]. Six questions refer to the functional status, including physical and social functioning and physical and emotional limitations. Four questions describe well-being including mental health, vitality and pain. One question relates to the overall health condition. In addition, seven questions are included measuring the duration and incidence of medical absenteeism and truancy as well as the reasons for it.

The *questionnaire at follow up (T1)* is similar to the baseline questions except for the exclusion of questions on fixed socio-demographic variables and the addition of questions about the satisfaction with the YHC professional consult.

The *YHC consultation questionnaire for students* consists of 11 items assessing the extent to which the YHC professionals have worked in accordance with the MASS protocol (exposure to intervention). In addition, 10 questions are included measuring the students’ appreciation of the consultation with the YHC professional. Finally students are asked to rate the entire consultation on a scale from 1 to 10, with 1 being the most-negative evaluation score and 10 being the most-positive one.

The *YHC consultation questionnaire for the YHC professionals* includes items assessing the extent to which the school (*N* = 4) and the YHC professionals (*N* = 11) work in accordance with the MASS protocol. In addition, the Dutch version of the self-sufficiency matrix (SSM-D) [40, 41] is completed by the YHC professionals. The SSM-D addresses the ability of students to provide for themselves regarding 11 specific life-domains (e.g. income, daytime activities, housing, mental health) as assessed by the YHC professional. Each life domain of the SSM is measured by a single item. On each item, students are evaluated on 5-point Likert-type scales, from ‘in crisis’ (1) to ‘thriving’ (5). Finally, the perceived value of the MASS intervention according to the YHC professional including the biological model and the SSM-D, is assessed.

